### Outcome measures

*Time points:* Assessments will be completed at baseline (immediately pre-randomisation), and 3 months and 12 months post randomisation by all participants. All time points will be taken into account during analysis, but the primary efficacy end point is 3-month follow-up. In order to justify treatment costs, clinically significant treatment effects need to be maintained over time, and this is particularly important in a chronic relapsing and remitting condition such as CLBP, so maintenance of any treatment effects will be assessed at 12 months. The RAs will be employed to coordinate the trial and collect baseline and follow-up data. All participants will be sent (emailed and posted) follow-up questionnaires by the RAs at 3 and 12 months. Participants not returning questionnaires within 1 week will receive a reminder email, telephone call and text in 3-day intervals. One week after that, if no data have been returned, the RAs will ring the participant to ask if they can collect primary outcome data over the telephone.

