### Planned interventions

#### Physiotherapy informed by Acceptance and Commitment Therapy

PACT is a brief physiotherapy intervention guided by principles of ACT designed to promote self-management, consisting of two 60 min face-to-face sessions 2 weeks apart, plus one booster telephone call (lasting 20 min), 1 month after the last treatment session. PACT alters the content of physiotherapy treatment and reconfigures it so that it is delivered in fewer but longer sessions, although the total contact time is similar to the average amount of time patients with CLBP receive as part of usual physiotherapy treatment as reported in two UK RCTs for CLBP, where usual physiotherapy was used as the control arm.^31^
^32^ Two 60-min sessions are designed to allow adequate time to do an initial physical assessment and provide feedback, create value-based goals, provide individualised physical exercises and teach simple psychological skills to promote psychological flexibility, and to address facilitators and barriers to self-management. The booster phone call promotes self-management by giving patients a chance to feedback progress and gain support with any ongoing issues they may have. PACT thus aims to directly reduce avoidance and promote openness, to build present-focused awareness, and coordinate greater engagement in goal-oriented and value-based activity (see box 1 below). The face-to-face intervention will be supported by a patient manual individualised to patient needs. Patients randomised to PACT will be given their patient manual during their first session.
Box 1Summary of the content of Physiotherapy informed by Acceptance and Commitment Therapy (PACT) sessions*PACT Session 1: 60 min face to face*

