### Participant identification and recruitment

In total, 240 patients will be recruited, 120 per treatment arm, over an 18-month period. Patients will be recruited from six secondary care physiotherapy clinics in London and the South East of England. Posters advertising the study will be placed in relevant physiotherapy clinics in order to inform patients and clinicians about the study. Potential participants referred to outpatient physiotherapy by their general practitioner (GP) or consultant will be identified by clinical physiotherapists from each hospital centre at their initial triage sessions, provided with written and verbal information about the PACT trial, and invited to participate. Participants who consent to be contacted will be referred to the research associates (RAs) for full eligibility screening, conducted by telephone. All patients who undergo screening will be recorded anonymously on a screening database associated with the study by the RAs. If the patient is suitable, the RA will then invite them to complete consent forms and baseline measures either at home online, via postal questionnaires or in person at the clinic (table 1). GPs will be notified in writing of their patient's participation. Patients will be informed that they can withdraw from the study at any time without giving a reason and that this will not affect the treatment they receive in any way. All participant responses will be anonymous and confidential, and participants will not be identified in any way by their responses (figure 1).

**Table 1 BMJOPEN2016011548TB1:** Screening and data collection across the trial: summary of the key trial processes from a potential participant agreeing to be contacted to the data collection time points

Process	Completed by	Format of administration	Pre-consent	Baseline	3-Month follow-up	12-Month follow-up	Ongoing during treatment period	Reference
Identification*	PT	PP	●					
Screening	RA	Telephone	●					
Consent	P	PP/DB		●				
Randomisation	CTU	CTU Database		●				
Sociodemographics	P	PP/DB		●				
EuroQol-5D-5L	P	PP/DB		●	●	●		36
Medical Outcomes Survey Short Form-12 (V.2)	P	PP/DB		●	●	●		37
Roland-Morris Disability Questionnaire	P	PP/DB		●	●	●		38
Chronic Pain Acceptance Questionnaire-8	P	PP/DB		●	●	●		39
Committed Action Questionnaire-8	P	PP/DB		●	●	●		40
Numeric Analogue Scale	P	PP/DB		●	●	●		–
Patient-Specific Function Scale	P	PP/DB		●	●	●		41
Work and Social Adjustment Scale	P	PP/DB		●	●	●		42

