Pain Self-Efficacy Questionnaire	P	PP/DB		●	●	●		43
Generalised Anxiety Disorder-7	P	PP/DB		●	●	●		45
Life Satisfaction Scale	P	PP/DB		●	●	●		–
Patient Health Questionnaire-9	P	PP/DB		●	●	●		46
Global improvement	P	PP/DB			●	●		47
Satisfaction with outcome	P	PP/DB			●	●		47
Treatment credibility	P	PP/DB			●	●		48
Health-related resource use	P	PP/DB		●	●	●		49
Self-reported adverse event	P	PP/DB			●	●		–
Clinician-reported adverse event	PT	PP/DB					●	–
Treatment attendance	PT	DB					●	–

*Includes permission to contact and provision of patient information letter.

CTU, King's Clinical Trials Unit; DB, online database; P, participant; PP, paper and pencil; PT, physiotherapist; RA, research associate.

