#### Adverse events

Any adverse events will be recorded by the treating physiotherapist in the clinical notes and reported to the RA and chief investigator immediately via email. Patients will also be offered the opportunity to report any adverse events on the follow-up questionnaires. If a patient becomes distressed during treatment, then the PACT physiotherapists will be adequately trained to deal with this or to identify a need for more input/support and refer them for an appropriate assessment. There will be clinical supervisors available at each research site if needed, and experienced psychologists will supervise physiotherapists delivering PACT on a monthly basis.

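### The fallback telephone call names only the primary outcome, so a patient who responds only by phone gives no self-reported adverse event answer for that time point

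*Protocol article*

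**What the plan says.** Outcome measures section: questionnaires are sent at 3 and 12 months after randomisation, with reminders by email, telephone and text. The next step is conditional: "One week after that, if no data have been returned", then "the RAs will ring the participant to ask if they can collect primary outcome data over the telephone". The primary outcome is the RMDQ. The section names nothing else for this call.

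Adverse events have two sources.

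- **Physiotherapist.** The Adverse events subsection states: "Any adverse events will be recorded by the treating physiotherapist in the clinical notes". In Table 1 the row "Clinician-reported adverse event" is marked only in the column "Ongoing during treatment period".
- **Patient.** The same subsection adds: "Patients will also be offered the opportunity to report any adverse events on the follow-up questionnaires". In Table 1 the row "Self-reported adverse event" is marked at 3 and 12 months, completed by the participant on paper or online.

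The Serious adverse events subsection sets out how a serious event is handled once it has been recorded. The intervention section describes PACT as "two 60 min face-to-face sessions 2 weeks apart, plus one booster telephone call (lasting 20 min), 1 month after the last treatment session".

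**The concern.** After physiotherapy contact ends, the follow-up questionnaire is the only route for adverse events that the protocol describes. The fallback call exists because that questionnaire was not returned, and it is specified for the RMDQ. The trial would then be speaking to a patient whose adverse event answer is missing without asking for it.

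At stake is how completely harms are counted after treatment. The review of serious events can act only on events that reach it. If return rates differed between arms, the harms comparison could be affected as well. PACT contact is short and fixed, whereas usual care has no fixed length, so PACT patients may come to depend on self-report sooner.

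**Working it through.** The plan gives no figure on this point to reproduce. The check is a reading of the follow-up procedure against Table 1 and the safety sections, followed by simple arithmetic on scale.

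**1. Which source covers which period**

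- During treatment: the treating physiotherapist (Adverse events subsection; Table 1, treatment-period column).
- After treatment: the self-report item at 3 and 12 months (same subsection; Table 1). No other route is described.

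**2. What the call collects**

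Table 1 shows paper or online for the self-report item, but it shows the same for the RMDQ, which the text does allow by telephone. The table's mode column therefore settles nothing. The point rests on the text of the call, which extends telephone collection to the primary outcome and mentions no other item.

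**3. Result by response pattern, following the text as written**

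- Questionnaire returned with the item completed: RMDQ and adverse event answer.
- No questionnaire, reached by phone: RMDQ, no adverse event answer.
- No questionnaire, not reached: neither.

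The second pattern is the one that the plan could change at little cost.

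**4. Length of the uncovered period for a patient who completes PACT on schedule**

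- From first session to booster call: 2 weeks + 1 month = about 1.5 months.
- Phone-only at both follow-ups: 12 − 1.5 = about 10.5 months.
- Phone-only at 12 months, form returned at 3 months: 12 − 3 = 9 months.
- Phone-only at 3 months, form returned at 12 months: 3 − 1.5 = about 1.5 months if the later form looks back only to month 3, and possibly nothing if it looks back further. The recall period is not stated.

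Treatment is counted from the first session and follow-up from randomisation. A wait of w months between the two shortens the first figure to 10.5 − w, so 10.5 is a maximum. No matching figure can be given for usual care, because its duration is not fixed.

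**5. Number of patients**

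The share who respond only by phone is not in the protocol. As an assumption:

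- 0.05 × 240 = 12
- 0.10 × 240 = 24
- 0.15 × 240 = 36

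These are counts per time point.

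**The case against.** The strongest case against is that the protocol does not say the call is limited to the primary outcome. The sample size section also says that a standardised follow-up procedure is still to be developed, and a call script is the kind of detail that an article leaves out. Part of this stands: the later procedure could add the item. But the article does state what the call is for, and it describes the later procedure in terms of standardising follow-up and recording contact details, with no sign of safety items.

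A second argument is that a minimal call is a reasonable way to rescue the primary endpoint from patients who have ignored several reminders. This supports asking the RMDQ first. It does not argue against one further item once the RMDQ is complete.

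A third concerns blinding. The research associates are to be blind to allocation, and a spoken account of an adverse event may reveal the treatment. Asking last protects that call's RMDQ, but not a 12-month RMDQ taken by the same associate by phone. This stands as a real, small cost. It is not new, because physiotherapist-reported events already go to the research associate by email.

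Four stronger readings are tempting, and the document does not support them:

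- *An event in a phone-only patient never reaches the serious event process.* Events during treatment can reach it through the physiotherapist, and a later returned form may supply an earlier event.
- *The loss falls only on patients reached by phone.* It arises from non-return and equally affects patients never reached. The call does not cause it; it is the contact at which the loss could be reduced.
- *The assumed 20% attrition (0.20 × 240 = 48) measures the problem.* That figure is a sample size assumption. The protocol does not link it to the reminders or to the call.
- *Non-returners are the patients who are unwell.* This is plausible, but nothing in the document shows it.

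**Conclusion.** The point holds, and it is modest. Followed as written, the procedure leaves a phone-only patient with an RMDQ score and no self-reported adverse event answer for that time point. Events after treatment may then go unrecorded unless a later form is returned.

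The conclusion rests on the plain reading of the call's content and on there being no post-treatment route beyond those described. Its size is uncertain: the patient counts are purely illustrative, and the longest gap requires a phone-only response at both follow-ups. The protocol describes the study as very low risk, and neither the primary estimate nor its power is touched. This is a cheap improvement in the ascertainment of harms, not a flaw that threatens the trial's conclusions.

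**What to change.** Amend the last step of the follow-up procedure in the Outcome measures section so that the call collects the RMDQ first and then the existing self-reported adverse event item. Use a short script that asks patients not to name their treatment. Route any event reported through the procedures already set out under Adverse events and Serious adverse events.

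The cost is one added line in the procedure, one added item on a call already planned, and a slightly longer call. The added unblinding risk matters mainly for a 12-month RMDQ taken by telephone. The script limits it, as does having a different research associate make the later call where one is available.

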### Baseline measures

Participants will complete a baseline assessment questionnaire which includes the validated scales detailed below, plus demographic data to establish sociodemographic characteristics of participants as follows: age, sex, height, weight, self-reported ethnicity, education level, employment and benefit status, diagnosis and history of any medical condition if available.

#### Primary outcome: the RMDQ

Patient-reported disability is recommended as a core outcome measure in low back pain^14^ and chronic pain trials.^50^ The Roland-Morris Disability Questionnaire (RMDQ)^38^ is a 24-item questionnaire assessing self-reported functioning and disability due to CLBP, ranging from 0 (no disability) to 24 (maximum disability). The RMDQ is a widely used and valid measure with good test–retest reliability. A 2–3 point change from baseline is considered clinically important.^51^

#### Secondary outcome measures

Secondary outcomes have been selected to determine the wider effects of PACT and to assess therapeutic processes and mechanisms of action. The outcomes include all core domains recommended in chronic pain research:^50^ pain, function, mood, QoL and satisfaction with treatment. A Global Improvement scale^47^ and Treatment Credibility^48^ Questionnaire will be completed at follow-up.

##### QoL: Work and Social Adjustment Scale (WSAS) and EQ-5D-5L

The Work and Social Adjustment Scale (WSAS) measures the effect of CLBP on participants' ability to work and participate in social and private leisure activities.^42^ The WSAS has five items scored from 0 (not affected) to 8 (severely affected), with a total possible score of 40. The EQ-5D-5L is the most frequently used tool for generating quality-adjusted life years (QALYs), which are favoured by the National Institute for Health and Care Excellence (NICE).^52^

##### Pain: pain Numeric Analogue Scale (NAS)

A single pain item rated using a numerical analogue scale anchored at 0 with ‘no pain’ and 10 with ‘worst possible pain’ will reflect the participants' subjective experience of pain.

##### Function: Patient-Specific Functional Scale (PSFS)

The PSFS is a self-reported measure used to identify and investigate functional status tailored to the patient.^41^ The patient identifies three activities limited by their CLBP, rating them on a scale of 0 (unable to perform activity) to 10 (able to perform activity at the same level as before injury/problem). The scores across the three items are summed to give a total possible score of 30.

##### Mood: Generalised Anxiety Disorder-7 (GAD-7) and Patient Health Questionnaire-9 (PHQ-9)

The GAD-7^45^ has seven items that assess anxiety in the last 2 weeks. Scores range from 0 to 21, with a total score of ≥8 indicating probable generalised anxiety disorder. The PHQ-9^46^ is a brief nine-item questionnaire that identifies and quantifies depressive symptoms; scores range from 0 to 27, with a total score of ≥10 indicating probable depressive disorder. Both questionnaires are well validated, commonly used self-report instruments for detecting distress, depression and anxiety in patients with medical illnesses.

#### Process variables

##### The Chronic Pain Acceptance Questionnaire-8 (CPAQ-8) and Committed Action Questionnaire-8 (CAQ-8)

Acceptance of pain and persistent but flexible behaviour towards achieving a goal form part of the ACT model and are therefore putative mediators of the efficacy mechanism in PACT treatment. The CPAQ-8^39^ is a shortened version of the original 20-item Chronic Pain Acceptance Questionnaire, which assesses the capacity to engage in activities without struggling with the pain. Each item is scored from 0 (never true) to 6 (always true), with a total possible score of 48. The CAQ-8^40^ is a shortened version composed of eight questions from the original 18-item Committed Action Questionnaire aimed to measure committed action in terms of commitment to valued goals. The items are rated from 0 (never true) to 6 (always true), with a total possible score of 48.

##### Pain Self-Efficacy Questionnaire (PSEQ)

The PSEQ^43^ assesses confidence in undertaking normal activities despite pain, which is an important variable to measure in interventions designed to enhance self-management. The questionnaire consists of 10 items rated on a 7-point scale anchored at 0 with ‘not at all confident’ and 6 with ‘completely confident’. Items are summed to generate a total possible score of 60.

#### Satisfaction: satisfaction with life, global improvement, treatment credibility

Satisfaction with treatment will be assessed by patients rating their overall improvement in terms of Patient Global Impression of Change (PGIC), their satisfaction with outcome and how credible they found their treatment.^47^ This has five items scored on 11-point scales ranging from 0 (not at all) to 10 (completely). Life satisfaction will be assessed by a single item: ‘All things considered, how satisfied are you with your life as a whole nowadays?’ Responses are on a scale from 0 (extremely dissatisfied) to 10 (extremely satisfied).

#### Health economics: EQ-5D-5L and SF-6D

This study is an important opportunity to pilot methods for estimating the economic impact of interventions on CLBP needed to design cost-effectiveness analyses (CEAs) in future definitive trials. Previously reported CEAs in the UK have relied on utility values derived from two different instruments—the EQ-5D-5L^36^
^52^
^53^ and the SF-6D.^18^ The EQ-5D-5L is the most commonly used tool for generating QALYs; however, the SF-6D, which is derived from scores obtained on the Medical Outcomes Survey Short Form-12 (v2), may be more sensitive to change in CLBP. The economic burden of CLBP is considerable from an NHS and patient perspective. A resource use questionnaire which identifies key cost drivers (NHS and non-NHS) will be developed based on previous studies. This will then be piloted to ensure completion rates, avoid redundant questions and to identify any additional resource use items sensitive to change in a CLBP population.^54^ This pilot study will compare the validity and sensitivity of the EQ-5D-5L (the most recent version of the EQ-5D) and the SF-6D for use in economic evaluations of cognitively enhanced physiotherapy for CLBP.

#### Adherence to PACT treatment

Patients' adherence to PACT treatment will be recorded by trial physiotherapists on a database. Attending both face-to-face sessions will be considered adherence to PACT treatment. In the UC arm, the type of treatment and attendance at physiotherapy sessions will be recorded by the trial physiotherapists on the database. Any modifications or departures from randomised treatments, withdrawal of participants from trial treatment or research follow-up will be recorded and reported as such.

#### Qualitative component

##### Patient interviews

A nested qualitative study will explore patients' experiences of PACT treatment. The aim of these methods will be to assess patients' views of the acceptability of PACT, to provide insight into the quantitative results and to explore processes of change. Semistructured face-to-face interviews will be conducted with up to 25 participants (sampled purposively to encompass a mix of gender, age, recruitment site and baseline RMDQ scores) following their 3-month follow-up assessment (RCT outcome primary end point). Interviews will be transcribed verbatim and analysed using thematic analysis^55^ to generate the key themes. Analysis will commence after the first interview in an iterative process, allowing early insights to be explored more fully in later interviews and topic guides to be amended as necessary. A reflexive diary will be kept during the recruitment, interview and data analysis process to ensure transparency of the analysis process. Respondent validity and independent coding by another researcher will be conducted to check the validity of emergent themes.

##### Physiotherapist interviews

Additional, nested, longitudinal, qualitative methods will explore the feasibility and acceptability of the PACT training programme for physiotherapists. All physiotherapists trained in PACT will be invited to attend individual face-to-face semistructured interviews by independent researchers. Later, the eight physiotherapists providing PACT treatment will be interviewed on two more occasions, 6 months after training and at the end of treatment delivery, to assess their perceptions of delivering this novel physiotherapy service treatment. All qualitative interviews will provide insight into the acceptability and feasibility of PACT, development of competency and any contextual factors linked to delivery to inform in any future research in this area.

Interviews will be conducted by independent researchers, transcribed verbatim and analysed using framework analysis to generate the key themes.^56^ Analysis will commence after the first interview in an iterative process, allowing early insights to be explored more fully in later interviews and topic guides to be amended as necessary. A reflexive diary will be kept during the recruitment, interview and data analysis process to ensure transparency of the analysis process. Respondent validity and independent coding by two researchers will be conducted to check the validity of emergent themes.

